## Abstract

**Background:**

Peripartum depression (PPD) is a serious public health issue associated with severe and potentially long-term adverse maternal and child developmental outcomes. Suicide and overdose, for example, accounts for up to a third of maternal deaths. A current depression diagnosis with no active treatment is a common risk factor for maternal suicide. Repetitive transcranial magnetic stimulation (rTMS) is a non-pharmacological treatment that has recently shown some promise as an effective treatment with limited side effects for PPD, but more research is required. This study aims to identify current barriers and potential facilitators for women with PPD accessing treatment in general, and rTMS specifically.

**Methods:**

This study will consist of two anonymous, self-administered surveys, focus groups, and interviews. A descriptive interpretative approach will be employed, and thematic analysis will be completed for the focus groups and interviews. Participants who are currently, or have previously experienced depressive symptoms, as well as health providers will be recruited. Our study will follow an equity, diversity, and inclusion (EDI) perspective on sex, gender, and ethnicity and the gender-based analysis plus (GBA+) analytic tool will be used. Both a qualitative and quantitative analysis of the data will be conducted.

**Discussion:**

We expect to find education and accessibility to be primary treatment barriers for persons with PPD. Identifying and addressing barriers is a critical first step towards the devolvement of initiatives that can work towards improving mental health in this population.

## Introduction

Peripartum depression (PPD) is a serious and often persistent disorder that negatively impacts the mother and child’s short-term and long-term health outcomes and presents a heavy societal burden (1). PPD refers to a major depressive episode with onset during pregnancy or within the first 4 weeks after delivery (2). Patients often experience persistent sadness and lack of interest, sleep and appetite disturbances, suicidal ideations and attempts, and difficulties in thinking and concentration (2).

Women suffering from PPD may experience worsening physical health (i.e., worse aerobic capacity) (1), increased healthcare utilization (1), worsening psychological health (i.e., increased anxiety, long-term depression, lower self-esteem, stress) (1, 3), lower quality of life (1, 4), impaired relationships (i.e., lower social functioning and support, distant and difficult partner relationships) (1), increased risk-taking behavior (i.e., smoking) (1, 5), and increased suicidal ideation with suicide being responsible for 8%–30% of maternal death (1, 6, 7).

Mother-infant bonding is also negatively impacted by PPD. A 2019 systematic review found that mothers with PPD were less emotionally available, warm, and sensitive toward their children (1). This withdrawn behavior and limited attachment can translate to poor child physical health (i.e., prolonged illness with diarrhea, increased pain response, more instances of night-time awakening) and impaired cognitive, social, language, emotional, and behavioral development (1). Another point of concern is the increased rate of mortality in this population of children. It’s been observed that probable postpartum depression was linked to a three-fold increase in the risk of infant death during the first 6 months after delivery and a two-fold increase during the first 12 months (8).

PPD is often treated through psychotherapy, pharmacotherapy, and electroconvulsive therapy (ECT) (9). Psychotherapy is often used to treat mild to moderate depression but demonstrates limited effectiveness when treating more severe and treatment-resistant forms of depression (10, 11). Pharmacotherapy is typically added to psychotherapy to increase treatment effectiveness (12). However, taking medication while pregnant or breastfeeding is considered unacceptable by many patients due to the potential effects it may have on their child (i.e., neonatal distress, preterm birth) (13, 14).

ECT is effective in treating resistant and life-threatening depression and is considered safe for use during pregnancy by the American Psychiatric Association and the American College of Obstetricians and Gynecologists (15). Yet, the surrounding stigma and its side effects (i.e., nausea, memory problems, muscle pain) limit the desirability and perceived acceptability of ECT treatment (16, 17). Additionally, receiving ECT while pregnant is associated with an increased risk for aortal compression and aspiration in the mother, and possible fetal heart rate changes (16).

There is a growing need for safe and effective treatments for persons suffering from PPD as evinced by the rising suicide rate, the constant rate of depression, the increasing disability associated with depression, and the limited acceptable treatment options available for this population (2, 3, 10–18).

Over the last two decades, repetitive transcranial magnetic stimulation (rTMS) has emerged as a promising effective and safe treatment option for treatment-resistant depression (TRD) (19, 20). rTMS is a non-pharmacological treatment that uses magnetic field pulses to elicit electrical current changes in the dorsolateral prefrontal cortex (DLPFC) (21). There is evidence that rTMS exerts antidepressant effects by causing recurrent and consistent firing of coactive cortical neurons, thereby potentiating plasticity in the cortex (22). Additionally, meta-plasticity, or the plasticity of synaptic plasticity, is thought to be modulated by non-invasive brain stimulation techniques such as rTMS and may also play a role in its therapeutic effects in depression (23). In 2002 and 2008, rTMS received approval from Health Canada and the US Food and Drug-Administration (FDA), respectively, as a treatment for TRD.

More recently, rTMS has been investigated as a treatment for PPD with onset during pregnancy (24–26) and during the postpartum period (27–30). Although limited, the current literature suggests that rTMS is an effective and safe treatment with minimal side effects. However, due to the small sample sizes and the paucity of randomized controlled trial data, more research is needed to further delineate the effectiveness of rTMS on patients with PPD.

Despite the availability and safety of rTMS as a treatment for PPD, there is a limited uptake in this population which begs the question “why aren’t more women with PPD receiving rTMS?” Understanding facilitators to treatment and barriers preventing women with PPD from accessing rTMS treatment is the first step toward ensuring that everyone can access safe and effective treatments. The limited literature assessing the knowledge, experiences, and attitudes of psychiatrists (31, 32), patients with depression (33), and pregnant women (34) towards rTMS treatment found insufficient knowledge and negative attitudes. More research is needed to identify current barriers and potential facilitators for women with PPD accessing treatment in general, and rTMS specifically. We expect to find insufficient knowledge on how to access mental health treatment during the peripartum period, limited awareness of the existence of rTMS treatment, and accessibility related concerns.

## Methods

### Objectives and purpose

Our research aims to identify barriers preventing women with PPD from accessing treatment generally, and rTMS treatment specifically. This will be accomplished by engaging with mental health professionals, adults who experienced depressive symptoms during the peripartum period, and adult members of their families. By connecting with these communities, we strive to better understand the concerns of participants and ascertain potential avenues for improving mental health service access and delivery. Our study will follow an equity, diversity, and inclusion (EDI) perspective on sex, gender, and ethnicity and the gender-based analysis plus (GBA+) analytic tool will be used.

### Ethics

This study received ethical approval from the University of Alberta Research Ethics Office (Pro00114151). Informed consent will be received from all participants. All participants will read through a consent form prior to the start of the study. Participants completing the survey will then select yes/no to four questions confirming they are 18 years or older, read and understood the information form, and consent to participating in the study. Prior to the start of the focus group, members of the research team will ensure everyone has read and understood the consent form and be reminded that their participation implies their consent. Participants in the interviews will give verbal informed consent during the recorded and transcribed interview. This consent procedure has been reviewed and approved under Pro00114151.

### Trial design

#### Participant recruitment

Participants will be recruited from multiple sources on both a local and national scale. Locally, recruitment posters will be hung at women’s health clinics, family doctor offices, pediatrician offices, psychologist or therapist offices, rTMS clinics, and universities. We will also reach out to local organizations to establish a partnership for recruitment (i.e., Canadian Mental Health Association, Alberta Council of Women’s Shelters, Terra Centre).

For national recruitment, we are partnered with the Mood Disorders Society of Canada who will share our surveys with their network. Additionally, we will recruit participants nationally through advertised social media posts (i.e., Instagram).

#### Equity, diversity, and inclusion

All participants will be asked to provide the following demographic information: gender, age, ethnicity, and the first three values of their postal code. This information will allow us to perform EDI based analyses assessing the impact these identity factors have on a person’s access to depression treatment during the peripartum period.

Our survey is translated by RCIC Certified Document Translation and Translators into several languages (i.e., French, Arabic, Mandarin, Punjabi) to increase its accessibility and allow us to explore culture-linked barriers/facilitators to treatment from an EDI perspective. To ensure the meaning of the survey questions is preserved through the translation process, the translated surveys were reviewed for accuracy and consistency by native language speakers. Survey translation allows for the capture of multiple viewpoints and aids in the inclusion of ethnically diverse populations.

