We completed an *a priori* power analysis through the G*Power 3.1 software and used an effect size of 0.15, an alpha error probability of 0.05, and a power of 0.95 (36). Our first survey directed to health professionals contains 10 predictors/variables and would require a minimum sample size of 172 participants. Our second survey directed to persons who experienced depressive symptoms during the peripartum period, and their families contains 15 predictors/variables and would require a minimum sample size of 199 participants. The survey will collect demographic and clinical data. Categorical data will be statistically analyzed using the chi-square test, numerical data will be analyzed using the multivariate analysis of variance (MANOVA), and continuous variables will be analyzed using independent and paired *t*-tests. All data analysis will be conducted using the Statistical Package for the Social Sciences (SPSS^®^; IBM^®^ SPSS^®^ Statistics Premium for Macintosh, Version 28.0, IBM Corp., Armonk, NY, United States).

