### Limitations

The online nature of our study presents a selection bias as not everyone has equal access and competency with online platforms (i.e., REDCap, ZOOM). To mitigate this, members of the research team will visit several local organizations and provide the opportunity and the means for eligible participants to complete the survey and present the option to conduct an in-person interview. A second limitation is the potential for recall bias. Since the various components of the study asked participants about past experiences with PPD treatment, it is possible that a participant may not accurately recall details of the experience or may be inclined to exaggerate or understate their experience. Finally, it is important to note that the proposed study will be conducted exclusively in Canada. Since a potential barrier to accessing rTMS treatment may be related to systemic and reimbursement-related issues, the generalizability of the findings may be limited. The Canadian healthcare system is primarily publicly funded with much of its services concentrated in urban areas. As such, the findings of our research may not fully capture the barriers and facilitators that would exist in a country that is more densely populated and/or fully relies on a private healthcare system, such as the United States of America (USA). However, due to the multiple avenues available to receiving rTMS in a Canadian context, this limitation is minimized. Although Canadian healthcare primarily follows a single-payer system, rTMS can also be accessed through private clinics that require out-of-pocket payments or can be partially or fully covered by private insurance plans, mimicking the characteristics of a private healthcare system.

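### The survey is meant to assess how each identity factor affects access to treatment, but for its multiple-choice items the plan names only the chi-square test, which cannot separate one factor from another

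*Protocol article*

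**What the plan says.** In the Protocol article, the section Equity, diversity, and inclusion lists the demographic items as "gender, age, ethnicity, and the first three values of their postal code" and gives their purpose: "EDI based analyses assessing the impact these identity factors have on a person’s access to depression treatment during the peripartum period".

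The Survey section describes the questions as multiple-choice items and rating scales. On analysis it states "Categorical data will be statistically analyzed using the chi-square test". It assigns MANOVA to numerical data, and independent and paired t-tests to continuous variables. It names no regression or stratified analysis, and it does not say which of these tests serves the equity analyses.

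The same section justifies the sample size. The authors "used an effect size of 0.15, an alpha error probability of 0.05, and a power of 0.95". The health-professional survey "contains 10 predictors/variables and would require a minimum sample size of 172 participants", and the patient and family survey "contains 15 predictors/variables and would require a minimum sample size of 199 participants".

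**The concern.** To speak of the impact of ethnicity on access, as distinct from that of age or place of residence, the analysis must consider the factors jointly. A chi-square test of a barrier item against ethnicity gives only the crude association. If ethnic groups differ in where they live, and place of residence drives the barrier, the test picks up residence and reports it as ethnicity. Residence is a credible confounder here, because the Limitations section itself says that Canadian services are concentrated in urban areas.

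A t-test compares two means and does not adjust either. MANOVA can hold several factors, but the plan reserves it for numerical data, so it does not cover multiple-choice outcomes.

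The section Gender-based analysis plus says the findings will inform recommendations for initiatives to improve access. A residence barrier read as an ethnicity barrier would point such an initiative at the wrong target.

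**Working it through.** **1. The plan's own sample sizes.** Inputs from the Survey section: effect size 0.15 (metric not named), alpha 0.05, power 0.95, and 10 or 15 predictors. Take the overall F-test of a multiple linear regression with k predictors and f² = 0.15. The numerator degrees of freedom are k, the denominator degrees of freedom are N − k − 1, and the noncentrality is 0.15 × N.

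| Survey | k | N | Denominator df | Noncentrality | Power |
|---|---|---|---|---|---|
| Health professionals | 10 | 172 | 161 | 25.80 | 0.9501 |
| Patients and families | 15 | 199 | 183 | 29.85 | 0.9507 |

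One respondent fewer gives 0.9486 (N = 171) and 0.9494 (N = 198), so 172 and 199 are exactly the minimum sizes under this model. A two-group MANOVA global test with 10 or 15 responses is the same F-test and gives the same two numbers.

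If 0.15 were instead read as the chi-square effect size w, 95% power would need 578 respondents at 1 degree of freedom and 1238 at 15. The stated sizes therefore do not come from the test named for categorical data.

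**2. Which named method can adjust, by type of data.**

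| Data type | Method named | Separates identity factors? |
|---|---|---|
| Categorical | Chi-square | No |
| Numerical | MANOVA | It can, if the factors are entered together |
| Continuous | Independent and paired t-tests | No |

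The gap is in the first and third rows. The first matters most, because multiple-choice items fall there.

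**3. How far a crude comparison can mislead.** The documents give no group shares or barrier frequencies, so all inputs here are assumptions. A barrier affects 60% of rural and 30% of urban respondents whatever their ethnicity. Group A is 40% rural and group B is 10% rural.

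- Group A: 0.40 × 0.60 + 0.60 × 0.30 = 0.42
- Group B: 0.10 × 0.60 + 0.90 × 0.30 = 0.33
- Spurious gap: 0.42 − 0.33 = 0.09

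The chance that a two-sided 5% test rejects is approximately Φ(0.09/SE − 1.96), where SE = √[0.42 × 0.58/n_A + 0.33 × 0.67/n_B].

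- 100 against 99: SE = 0.0683, so Φ(1.317 − 1.96) = Φ(−0.643) = 0.26
- 20 against 179: SE = 0.1158, so Φ(0.777 − 1.96) = Φ(−1.183) = 0.12

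**4. A milder assumed case.** The barrier is met by 25% of urban and 50% of rural respondents, and the groups are 90% and 60% urban.

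- First group: 0.90 × 0.25 + 0.10 × 0.50 = 0.275
- Second group: 0.60 × 0.25 + 0.40 × 0.50 = 0.350

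The gap is 7.5 points, and the test rejects about 21% of the time with 100 against 99.

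Across these cases the rejection rate is 12% to 26%, where an ethnicity test with no confounding would reject 5% of the time.

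**The case against.** The strongest reply is that crude disparities are what the study wants. The Discussion asks for light on differences across populations of responders, and a crude difference answers that. Place of residence may also lie on the path from ethnicity to poor access, so adjusting for it can remove part of the disparity of interest. This stands as a reason not to report adjusted figures alone. It does not rescue a plan that speaks of the impact of each factor and names no method that can separate them. Reporting both estimates meets the objection.

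A second reply is that MANOVA can hold several factors. That is true, and rating scales treated as numerical could be analysed that way. It does not reach the multiple-choice items. The sample sizes also reproduce as a two-group MANOVA, so the mismatch with the sizing is not proof that a regression was intended. On either reading, the sizing is not that of the chi-square analysis.

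Third, every confounding input is assumed, and the effect shrinks when one group is small. That also stands: the figures show what can happen, not what will. Finally, recommendations will also draw on focus groups and interviews, so they would not rest on these tests alone.

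**Conclusion.** The point holds for the multiple-choice access and barrier items. The stated aim needs a joint analysis of four factors, and the test named for those items gives only crude associations. With no true ethnicity effect, the assumed scenarios give a spurious gap of 7.5 to 9 points and a rejection rate of 12% to 26%. Separately, the sample size rests on a 10- or 15-predictor F-test (or the equivalent two-group MANOVA), while no regression is named.

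A reader might infer more, but the documents do not support it:

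- **False positives from many tests at 0.05.** That level is stated only for the power calculation. The number of comparisons is not given, and a multiplicity rule may sit in an analysis plan that is not shown.
- **Chi-square failing in sparse cells.** The ethnicity categories and group shares are not given, and the article does not say that raw postal codes will be used as categories. Grouping rules may also be set in the plan not shown.
- **Items missing from the survey.** The Objectives section says "Our study will follow an equity, diversity, and inclusion (EDI) perspective on sex, gender, and ethnicity", and the demographic list has gender but not sex. The Limitations section notes that "rTMS can also be accessed through private clinics that require out-of-pocket payments", and the list has no item on ability to pay. The questionnaire is in supplementary material that is not shown and may contain both.

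**What to change.** In the Survey section, replace the stand-alone chi-square test for the equity analyses. For each key access outcome in the patient and family survey, fit one logistic regression (ordinal where the outcome is ordered). Enter gender, age, ethnicity in collapsed categories, and residence together, with residence coded as urban/rural or province derived from the postal code. Use Firth or exact methods where counts are small. Report crude and adjusted odds ratios side by side with 95% confidence intervals, and label these comparisons exploratory.

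State which model and effect-size metric the 172 and 199 refer to, so that sizing and analysis agree. Those sizes already give 95% power for the overall test of a joint linear model at f² = 0.15. Logistic models would need their own check.

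The model uses only data already listed for collection. The cost is more analysis work and somewhat wider intervals for the adjusted estimates.

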#### Gender-based analysis plus

The GBA+ tool was created by the Canadian Government to aid in the establishment of initiatives that are equitable, diverse, and inclusive of the cultural mosaics that shape our communities. The GBA+ analytic process can be divided into five major steps: (1) identify the issue, (2) challenge assumptions (unconscious bias), (3) gather facts, research, and consult, (4) develop options and make recommendations, and (5) monitor and evaluate. The GBA+ analytic tool informed our study design and will be used as we assess our findings and create recommendations for initiatives to improve patients with PPD’s access to treatment.

#### Survey

We will conduct two national anonymous, self-administered, five-minute online surveys shared through REDCap (35). REDCap is an electronic data capture tool hosted and supported by the Women and Children’s Health Research Institute at the University of Alberta. The literature was reviewed by research team members for pertinent survey questions assessing participants’ experiences, attitudes, and recommendations for rTMS. Then two surveys were created, through group discussion and consensus, that are an amalgamation of the search results and the research team’s insight. The survey assesses participants’ experiences with, and barriers to, rTMS treatment through a mix of multiple-choice questions and rating scales. One of the surveys will be completed by health professionals (i.e., primary care physicians, therapists, psychiatrists, psychologists, residents, and nurses), and the other will be completed by adults who experienced, or are experiencing, depressive symptoms during the peripartum period and their families (see Supplementary materials for survey questions. The survey can be shared and completed through this link: https://redcap.link/a8kchdcn).

Since there are no similar previously validated surveys, we underwent a one-month “trial period” where we began recruitment for the English version of the survey to assess its performance and make any necessary modifications prior to the release of the multi-language survey on a larger scale.

We completed an *a priori* power analysis through the G*Power 3.1 software and used an effect size of 0.15, an alpha error probability of 0.05, and a power of 0.95 (36). Our first survey directed to health professionals contains 10 predictors/variables and would require a minimum sample size of 172 participants. Our second survey directed to persons who experienced depressive symptoms during the peripartum period, and their families contains 15 predictors/variables and would require a minimum sample size of 199 participants. The survey will collect demographic and clinical data. Categorical data will be statistically analyzed using the chi-square test, numerical data will be analyzed using the multivariate analysis of variance (MANOVA), and continuous variables will be analyzed using independent and paired *t*-tests. All data analysis will be conducted using the Statistical Package for the Social Sciences (SPSS^®^; IBM^®^ SPSS^®^ Statistics Premium for Macintosh, Version 28.0, IBM Corp., Armonk, NY, United States).

